#### Secondary — immunogenicity

#### Measles

Measles SNA titres by plaque reduction neutralization test (PRNT)Measles serum IgG binding antibody concentrations by a bead-based multiplex assay

#### Rubella

Rubella SNA titres by indirect immunocolorimetric assay (ICA)Rubella serum IgG binding antibody concentrations by bead-based multiplex assay

#### Adults and toddlers

Geometric mean fold rise (GMFR) in measles and rubella SNA titres and IgG concentrations from baseline to day 42 following study product administrationPercentage of participants undergoing seroconversion or experiencing a four-fold rise in measles and rubella SNA titres and measles and rubella IgG concentration between baseline and day 42 following study product administrationPercentage of measles and rubella seroprotected participants based on SNA titres and IgG concentrations on day 42 and day 180 following study product administrationMeasles and rubella SNA GMT and measles and rubella IgG geometric mean concentrations (GMC) day 42 and day 180 following study product administration

#### Infants

Percentage of participants undergoing seroconversion or experiencing a four-fold rise in measles and rubella SNA titres and measles and rubella IgG concentration between baseline and day 42 following study product administrationPercentage of measles and rubella seroprotected participants based on SNA titres and IgG concentrations on day 42 and day 180 following study product administrationMeasles and rubella SNA GMT and measles and rubella IgG GMC day 42 and day 180 following study product administration

#### Exploratory

To enumerate and characterize the measles and rubella-specific T-cell responses generated by MRV-MNP and MRV-SCTo describe the experience of participants and parents following study product administration by MNP compared to SC injectionTo describe the views of trial personnel regarding study product administration by MNP and to SC injection

### Participant timeline {13}

The participant timeline is shown in Table 1.

**Table 1 Tab1:** Participant timeline

Visit #	V0	V1	Home visits	V2	V3	V4	V5
Study day	−14 to −1	0	1 to 13	7	14	42	180
Visit window (days)	-	-	-	+2	+3	+14	+28
Written informed consent	X						
History and physical examination	X	X		X	X	X	X
Vital signs and anthropometry	X	X		X	X	X	X
Screening and safety labs	X			X	X^a^		
Serum pregnancy test^b^	X						
Urinary pregnancy test^b^		X					X
Malaria rapid diagnostic test/blood film	X	X					
Immunogenicity blood samples	X					X	X
Final confirmation of eligibility		X					
Randomization and study product administration		X					
Solicited local and systemic AE data collection		X	X	X	X		
Unsolicited AE collection		X	X	X	X	X	X
EPI vaccine administration^c^						X	
T-cell responses — exploratory	X			X		X	X
Participant/parent experience — exploratory		X X^d^			X	X	
End of study							X‖

^a^Adult cohort only; ^b^adult females only; ^c^toddlers and infants will be administered the other EPI vaccines due at 15 to 18 months and 9 to 10 months/12 months respectively at V4 (day 42);^d^pre-vaccination (may also be conducted at V0) and post-vaccination; ‖toddlers and infants will be administered an additional SC dose of a measles and rubella vaccine on or after the end of study visit outside the current protocol to ensure protection based on the current EPI schedule in The Gambia

### Sample size {14}

The sample size has not been determined by a power calculation based on testing a formal statistical hypothesis. Instead, it has been chosen to provide the required descriptive data on the safety and tolerability of the MRV-MNP to guide decisions regarding product development and to provide supporting information regarding the immunogenicity of the MRV-MNP.

#### Safety and tolerability

Table 2 indicates the probability that a given safety event will occur at least once or at least twice based on true event rates in the vaccinated population of between 1 and 20% based on the different sample sizes (*n*).

**Table 2 Tab2:** The probability of any given safety event occurring at least once or at least twice given a true population event rate of between 1.0 and 20.0% according to the indicated samples sizes per group

True event rate (%)	*n* = 30		*n* = 60		*n* = 150	
	Probability of at least 1 event	Probability of at least 2 events	Probability of at least 1 event	Probability of at least 2 events	Probability of at least 1 event	Probability of at least 2 events
20	99.9	98.9	100.0	100.0	100.0	100.0
10	95.8	81.6	99.8	98.6	100.0	100.0
7.5	90.4	66.9	99.1	94.5	100.0	100.0
5	78.5	44.6	95.4	80.8	100.0	99.6
2.5	53.2	17.2	78.1	44.4	97.8	89.1
1	26.0	3.6	45.3	12.1	77.9	44.3

A sample size of 30 (adult) participants provides a probability of 95.8% that at least one episode of a given safety event will occur and a probability of 81.6% that at least two episodes of an event will occur based on a true event rate of 10% in the vaccinated population. The same sample size provides probability of 78.5%, 53.2% and 26.0% that at least one event will occur given a true event rate of 5%, 2.5% and 1% in the population. If a given safety event does not occur in 30 adult participants, we can be 95% confident that the true event rate in the population is less than 11.4%.

A sample size of 60 (toddler or infant) participants provides a probability of 99.8% that at least one episode of a given safety event will occur and a probability of 98.6% that at least two episodes of an event will occur in each of the given cohorts based on a true event rate of 10% in the vaccinated cohort. The same sample size provides probability of 95.4%, 78.1% and 45.3% that at least one event will occur given a true event rate of 5%, 2.5% and 1% in the cohort. If a given safety event does not occur in a cohort, we can be 95% confident that the true event rate in that cohort is less than 6.0%.

A sample size of 150 participants receiving the MRV-MNP overall provides a probability of close to 100.0% that at least two episodes of an event will occur in the whole study population based on a true event rate of 10% in the vaccinated cohort. The same sample size provides probability of close to 100.0%, 97.8% and 79.9% that at least one event will occur given a true event rate of 5%, 2.5% and 1% in the cohort. If a given safety event does not occur in a study, we can be 95% confident that the true event rate in that cohort is less than 2.5%.

Table 3 indicates the expected precision surrounding the estimates of given safety event rates in each cohort and in all participants who will receive MRV-MNP during the study. For example, if a fever (or any other event) is recorded in 5% of all participants who receive the MRV-MNP, we will be 95% confident that the true frequency of fever related to MRV-MNP administration lies between 2.5 and 9.8%.

**Table 3 Tab3:** Expected precision around the given safety event rate estimates in adults, toddler/infants and the whole population who will receive MRV-MNP

Event rate in sample (%)	***n*** = 30	***n*** = 60	***n*** = 150
	Event rate (%) (95% CI)	Event rate (95% CI)	Event rate (95% CI)
20.0	20.0 (9.5–37.3)	20 (11.8–31.8)	20.0 (14.4–27.1)
10.0	10.0 (3.5–25.6)	10 (4.7–20.2)	10.0 (6.2–15.8)
7.5	7.5 (22–22.4)	7.5 (3.1–17.0)	7.5 (4.3–12.9)
5.0	5.0 (1.2–19.1)	5.0 (1.7–13.7)	5.0 (2.5–9.8)
2.5	2.5 (0.3–15.4)	2.5 (0.6–10.1)	2.5 (1.0–6.4)
1.0	1.0 (0.0–13.1)	1.0 (0.1–7.8)	1.0 (0.2–4.2)

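### The sample size text gives 79.9% for seeing at least one 1% event in 150 recipients, where Table 2 and the binomial give 77.9%; one Table 3 interval also excludes its own estimate

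*Protocol article*

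**What the plan says.** Under Sample size {14}, the protocol article says that the sample size does not come from a power calculation and was chosen to give descriptive safety data and supporting immunogenicity data. The safety part is then set out in two tables with accompanying text.

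- Table 2 is described as "The probability of any given safety event occurring at least once or at least twice given a true population event rate", for groups of 30, 60 and 150. For 150 participants and a true rate of 1% it prints 77.9% for at least one event and 44.3% for at least two.
- The text on the whole trial begins "A sample size of 150 participants receiving the MRV-MNP overall provides a probability of close to 100.0" and goes on to the chance of at least one event at lower rates. It ends with "97.8% and 79.9% that at least one event will occur given a true event rate of 5%, 2.5% and 1% in the cohort".
- Table 3 gives 95% intervals around observed rates. Its worked example is a 5% rate among all 150 recipients, for which "we will be 95% confident that the true frequency of fever related to MRV-MNP administration lies between 2.5 and 9.8" per cent. For an observed 7.5% in 30 participants, the table prints a lower limit of 22 and an upper limit of 22.4.

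**The concern.** The text and Table 2 give different values for one quantity: the same group size, the same true rate and the same definition of the event. They cannot both be right, and the text has the more favourable one. This figure describes how likely the whole trial is to show at least one case of an uncommon reaction to a product not previously used in humans, so a reader may well take it from the text and repeat it.

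The Table 3 cell is a different kind of slip. A confidence interval for a proportion should contain the observed proportion, and an interval from 22 to 22.4 does not contain 7.5. The cell belongs to the column for 30 participants, which is the number of adults who receive the MRV-MNP.

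**Working it through.** **Inputs.** The number of MRV-MNP recipients is 30 adults + 60 toddlers + 60 infants = 150 (Trial design {8}). The true rates of 5%, 2.5% and 1% come from the Sample size {14} text and Table 2. The 95% level comes from Table 3.

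**Detection probability.** The chance of at least one event in n independent participants at true rate p is 1 − (1 − p)^n.

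| True rate | Formula, n = 150 | Result | Table 2 | Text |
|---|---|---|---|---|
| 5% | 1 − 0.95^150 | 99.95% | 100.0% | close to 100.0% |
| 2.5% | 1 − 0.975^150 | 97.76% | 97.8% | 97.8% |
| 1% | 1 − 0.99^150 | 77.85% | 77.9% | 79.9% |

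The first two figures in the text reproduce, so the text uses the same method as the table. Only the third fails. The gap is 79.9 − 77.9 = 2.0 points as printed, or 2.05 points against the unrounded binomial value.

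Two other routes to 79.9% were tried:

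- The Poisson approximation, 1 − exp(−1.5), gives 77.7%, which is further away.
- A different group size would have to be ln(1 − 0.799) / ln(0.99) = 159.6, or about 160 recipients. The design has 150.

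The remaining cells of Table 2, for 30, 60 and 150 participants, agree with the binomial to within 0.1 point. The isolated figure in the text is therefore the wrong one.

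**Table 3 cell.** The method has to be inferred, because the section does not name it. The Wilson score interval is

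(p + z²/2n ± z·√(p(1 − p)/n + z²/4n²)) / (1 + z²/n), with z = 1.96.

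It reproduces neighbouring cells. For n = 30 it gives 9.51 to 37.31 at 20% (printed 9.5 to 37.3) and 3.46 to 25.62 at 10% (printed 3.5 to 25.6). The exact Clopper-Pearson interval does not: at 20% it gives 7.71 to 38.57.

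For n = 30 and p = 0.075:

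- z²/n = 3.8415/30 = 0.1280, so the denominator is 1.1280.
- The centre is (0.075 + 0.0640)/1.1280 = 0.1232.
- The half-width is 1.96 × √(0.0023125 + 0.0010671)/1.1280 = 0.1010.
- The limits are 2.22% and 22.43%.

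The printed upper limit of 22.4 is right. The lower limit should read 2.2. Clopper-Pearson would give 1.1 to 23.2, so neither method produces a lower limit of 22.

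**The case against.** The strongest reply is that this is erratum-level. The correct 77.9% is already printed in Table 2, in the same section. The gap is 2 points in one descriptive probability. No hypothesis test is planned, the sample size was not set by a power calculation, and the pause rules and the data monitoring committee's reviews do not use the figure. All of that stands, and it fixes the weight of the point. It does not remove the contradiction between the text and the table.

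On the Table 3 cell, the reply is that the text was read from a PDF by a program and a decimal point may have been lost. That cannot be excluded, although the upper limit in the same cell kept its point. If the published table reads 2.2, this part falls away. If it reads 22, it is an obvious misprint that nobody would plan on.

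Three stronger readings are tempting, and the documents do not support them.

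- A reader might infer that the sample size justification fails. It does not. The justification spans Tables 2, 3 and 4 and three bounds for the case of no events; each paragraph on detection leads with the 10% rate, and no target is set for the 1% rate.
- A reader might infer that the tables are unreliable throughout. A few other limits do differ from Wilson in the last digit. For example, 9.746 is printed as 9.8 and 0.36 as 0.3. Differences of this size carry no consequence and are not part of this point.
- A reader might object that 7.5% of 30 is 2.25 people, which cannot be observed. Nominal rates are an ordinary planning convention, and the other columns also imply fractional counts (5% of 150 is 7.5). Listing attainable counts would be a preference and would not correct an error.

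**Conclusion.** The point holds as a minor correction. The text overstates the probability of at least one event among 150 recipients at a true rate of 1% by 2 points: 79.9% against 77.9%. Put the other way, the chance of seeing no such event is 22.1%, where the text implies 20.1%. This rests only on the binomial model that Table 2 itself uses, and the document's own table settles which value is right.

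The Table 3 cell is impossible as it appears here. That finding depends on the text having been read correctly from the PDF, and the replacement value of 2.2 depends on the Wilson method inferred from the neighbouring cells.

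Neither error changes the number of participants, the design, the analysis or any decision rule.

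**What to change.** 1. In the Sample size {14} text on the 150 recipients, change 79.9% to 77.9%, so that it agrees with Table 2.
2. Check the published Table 3. If the row for 7.5% and n = 30 does print a lower limit of 22, change the entry to 7.5 (2.2–22.4).

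The cost is at most two numbers in the text and a table. One stated probability becomes slightly less favourable, and nothing in recruitment, conduct or analysis needs to change.

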#### Immunogenicity

Table 4 indicates the expected precision surrounding the estimates of given immune response rates in each cohort. For example, if the immune response rate in adults vaccinated with MRV-MNP is 60%, we will be 95% confident that the true immune response rate in adults lies between 42.3 and 75.4%. Similarly, if the immune response rate in infants is 80%, we will be 95% confident that the true immune response rate in infants lies between 68.2 and 88.2%.

**Table 4 Tab4:** Expected precision around the given immune response (seroconversion or fourfold titre/concentration rise) rate estimates in adults and toddler/infants who will receive MRV-MNP

Immune response rate in sample (%)	***n*** = 30	***n*** = 60
	Immune response (%) (95% CI)	Immune response (%) (95% CI)
20.0	20.0 (9.5–37.3)	20.0 (11.8–31.8)
40.0	40.0 (24.6–57.7)	40.0 (28.6–52.6)
60.0	60.0 (42.3–75.4)	60.0 (47.4–71.4)
80.0	80.0 (62.7– 90.5)	80.0 (68.2–88.2)
100.0	100.0 (88.7–100.0)	100.0 (94.0–100.0)

### Recruitment {15}

#### Sensitization

Effective community and individual sensitization prior to trial initiation are key to trial recruitment and retention.

#### Community sensitization

Prior to any other activities taking place, a series of ‘kolanut’^1^ meetings with key leaders within the local community including the Alkalo (village/community leader), other community elders, religious leaders, members of women’s and mother’s groups and other community advocates will be undertaken at venues within the local area. During these meetings, details regarding the trial will be discussed and a chance given for questions to be asked to ensure everybody present gains a full understanding of the purpose of the trial and other key information (e.g. risks and benefits). The information provided will be based on the ICD to ensure the accuracy and consistency of the information given.

Following these meetings, information regarding the trial will be disseminated within the local community through well-established community networks. The meetings also serve a critical role in ensuring influential members of the community properly understand the trial and therefore that accurate information is passed on and misunderstanding is avoided. Feedback received during these meetings also assists the trial team in planning individual sensitization activities.

To recruit females using effective birth control, information will also be provided to staff of local family planning clinics so they can refer anyone who may be interested to the trial team. Toddlers and infants will predominantly be recruited through the government EPI clinics; therefore, the officers in charge of local health facilities as well as the public health officers who coordinate the clinics will be sensitized in the same way.

#### Individual sensitization

Individual sensitization involves the direct provision of more detailed information regarding the trial to those expressing potential interest in participation. During individual sensitization, members of the clinical trial team will provide a summary of the information in the approved ICD. At the end of this process, those who continue to express an interest in participating/having their children participate will be provided with the ICD and encouraged to discuss the trial with their partner, parent(s) and any other family members. Basic contact information including telephone numbers and a description of their place of residence will also be collected at this point to allow subsequent follow-up. In the case of the toddler and infant cohorts, the trial team will always speak directly by telephone or face-to-face with the second parent (unless there is no partner/second parent involved in the child’s care) and confirm they are also supportive of trial participation before formal informed consent takes place.

## Assignment of interventions: allocation

### Sequence generation {16a}

Randomization will be based on a pre-established computer-generated permuted block randomization scheme. Randomization will be stratified by sex although no fixed proportions of males and females will be required in any cohort. The block size will not be known to anyone involved in trial conduct.

### Concealment mechanism {16b}

Randomization will be undertaken using an in-house web-based electronic central randomization system to which only those unblinded staff undertaking randomization will have access. The system includes an audit trail which indicates who undertook randomization. The allocation sequence is concealed and the group to which a participant has been randomized only indicated after their subject number and eligibility for randomization has been confirmed.

### Implementation {16c}

The randomization scheme will be generated by a statistician not otherwise involved in the trial. Following screening and final confirmation of eligibility by a trial clinician, a unblinded member of the clinical trial team will undertake randomization. Having completed randomization, the same unblinded site personnel will prepare the appropriate MNP (MRV or placebo) and corresponding SC injection for administration.

The MRV-MNP and PLA-MNP are indistinguishable in appearance; thus, only the label of the primary packaging will be covered with an opaque label in this case.

The MRV and 0.9% sodium chloride for SC injection will be drawn into identical syringes for administration. However, given they may differ in colour slightly, once the injection has been drawn into the syringe and is ready for administration, the barrel of the syringe will be wrapped with opaque tape, masking the fluid, and ensuring the syringes are indistinguishable in appearance.

The MNP in its primary packaging and the syringe containing the SC injection will then be handed in a blinded fashion to blinded study personnel who will administer the vaccine.

In this way, the participants/parents as well as the staff administering the vaccine and all staff collecting endpoint data will be blinded to the study products administered.

The unblinded trial staff, who will also be responsible for all vaccine handling, storage and accountability procedures, will be restricted in number to ensure the integrity of the blind at the site. They will have no role in endpoint assessment.

All randomization and vaccine accountability procedures, including all documentation related to these processes, will be maintained in an area under separate access control. Access will be limited strictly to the unblinded team.

## Assignment of interventions: blinding

### Who will be blinded {17a}

The use of the double-dummy design, in which all participants receive an identical MNP and SC injection, ensures that the personnel applying the MNP and administering the SC injection, the participants/parents of participants, all staff involved in safety and other data collection, laboratory staff and staff involved in data management and analysis will be blinded to treatment allocation.

### Procedure for unblinding if needed {17b}

In the event of a medical emergency, the principal investigator (or designee) may require that the blind be broken for the participant experiencing the emergency when knowledge of the participant’s treatment assignment may influence the participant’s clinical care. The electronic central randomization system allows for unblinding under these circumstances under separate access control provide to the principal investigator.

If unblinding is required, every effort will be made not to unblind the participant/parent unless it is considered necessary for their welfare. In addition, the number of investigator staff who are unblinded will be minimized under such circumstances.

## Data collection and management

### Plans for assessment and collection of outcomes {18a}

#### Safety

#### Definitions

##### Adverse event

Based on ICH-GCP E6 (R2), an AE in this trial is defined as any untoward medical occurrence in a participant administered a study product which does not necessarily have a causal relationship with the study product itself. An adverse event can therefore be any unfavorable and unintended sign (including an abnormal laboratory finding), symptom or disease temporally associated with the administration of the study product whether related to the study product or not. Symptoms, signs or conditions present at screening (visit 0) which do not change are not AE and will be recorded as part of the screening procedures. Any subsequent change in the severity of a symptom, sign or condition following screening will be recorded as AE.

##### Serious adverse event

An AE is defined as serious if it:Results in deathAny deaths will be reported as grade 5 severityIs life threateningThe term life-threatening in the definition of serious refers to an event in which the participant was at risk of death at the time of the event; it does not refer to an event which hypothetically might have caused death if it was more severe.Requires inpatient hospitalization or prolongation of existing hospitalizationResults in persistent or significant disability/incapacityIs a congenital anomaly/birth defect

##### Important medical event

Important medical events that may not be immediately life threatening or result in death or hospitalization, but which may jeopardize the participant or may require intervention to prevent one of the other outcomes listed in the definition of serious should be reported in the same ways as serious adverse events.

